### Statistical analysis

Decisions about sample size and design of the project are primarily aimed at comparing the EG with the CSG. The main statistical analyses will be variants of analyses of variance such as Multivariate ANOVA (MANOVA) to test overall group differences, repeated measures ANOVA to look for interactions between time and group (i.e. to test whether the EG have larger change between time points than CSG). Changes in outcome measures will be correlated with changes in CRF. Analysis of covariance will be used to test hypotheses whether the effect of specific variables extend beyond effects of nonspecific variables. Baseline data could be analyzed without referral to later group membership, enabling analyses of empirically derived subgroups such as participants scoring low or high on the physiological measures, or participants with or without concurrent tobacco use. Baseline data will also be analyzed with regression analyses and correlations/partial correlations controlling for potential confounding variables.

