### Sample size calculations

We assume that the outcome measures are continuous variables with a normal distribution, and two independent clinical groups are being compared. Estimates of statistical power are calculated for the primary outcome measure. The neurocognitive tests applied in the study (MCCB battery) are designed for repeated administrations to test possible treatment effects. Some improvement must be expected in both groups because of the treatment/stimulation and as retest effects (being accustomed to the test design if not the actual test material). Nevertheless, we expect that the effect size in the EG will be 0.50 standard deviations (which is a medium effect size) *larger* than the increase in the CSG, which given a statistical power of 0.80 and alpha of 0.05 necessitates a sample size of 55 in each group. The dropout rate in the current study after randomization and group assignment is estimated to 15 %. Thus, the estimate is that recruitment of 126 participants is needed to secure the participation of 55 individuals in each group. Further attrition at later stages in the study progress is accounted for by utilizing the “intention-to treat” analysis.

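### The primary arm comparison would be better specified as a baseline-adjusted difference at T1: the MANOVA gives no single estimate of the sized contrast, and the group-by-time ANOVA is less precise

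*Protocol article*

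**What the plan says.** Under Sample size calculations, the protocol article treats the design as one in which "two independent clinical groups are being compared". The target is a difference in improvement between the arms: "we expect that the effect size in the EG will be 0.50 standard deviations" above the gain in CSG. The resulting group size is stated in these terms: "given a statistical power of 0.80 and alpha of 0.05 necessitates a sample size of 55 in each group". No visit, baseline covariate or correlation is named, and the article does not say whether the SD is that of the score or of its change.

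Under Statistical analysis: "The main statistical analyses will be variants of analyses of variance such as Multivariate ANOVA (MANOVA) to test overall group differences". The same sentence adds a repeated measures ANOVA for the interaction of time and group, explained as a check on whether change is greater under exercise. ANCOVA has a different role: "Analysis of covariance will be used to test hypotheses whether the effect of specific variables extend beyond effects of nonspecific variables".

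Under Assessments, the cognitive battery (MCCB) is scheduled at T0, before randomisation, at T1 (12 weeks) and at T2 (28 weeks). Changes are described in pairs, T0 to T1 and T1 to T2. Neurocognitive tests gives the battery seven domains.

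**The concern.** The sample size rests on one contrast between two groups, but the analysis section names two families of test. The MANOVA is an omnibus test. A significant result says that the arms differ somewhere, without giving one effect size and interval for how much more EG improved. The interaction test can give that estimate, but as described it makes no use of the baseline score as a covariate. In a randomised trial with a baseline measure on everyone, leaving it out gives up precision. At stake is some power, in a trial whose group size already gives less than 0.80 for a two-sided test of change if 0.50 is in change-score SDs, and a clear primary estimate.

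**Working it through.** **Inputs.** Difference 0.50 SD, power 0.80, alpha 0.05 and 55 per group come from Sample size calculations. The article gives no T0–T1 correlation, so ρ from 0.5 to 0.9 is assumed. Equal variances at the visits are assumed, and compound symmetry for the three-visit case.

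**The plan's own figure.** For two independent groups, n = 2(1.960 + 0.842)²/0.50² = 62.8, so 63 per group two-sided (64 by the t test). One-sided, it is 50 (51 by the t test). The stated 55 matches neither. At 55 per group, two-sided power by the t test is 0.74. That mismatch is a separate matter, but 0.74 is the benchmark here.

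**Precision.** In units of the score variance:
- change score: 2(1 − ρ)
- ANCOVA at T1 with baseline as covariate: 1 − ρ²
- ratio: (1 − ρ²)/[2(1 − ρ)] = (1 + ρ)/2, which is below 1 whenever ρ < 1.

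A group-by-time test on T0 and T1 alone is identical to a t test on the change score, so the change columns below also describe it.

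**Two-sided power at 55 per group**

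| ρ | (1+ρ)/2 | Change, 0.50 in change SD | ANCOVA, 0.50 in change SD | Change, 0.50 in score SD | ANCOVA, 0.50 in score SD |
|---|---|---|---|---|---|
| 0.5 | 0.75 | 0.74 | 0.85 | 0.74 | 0.85 |
| 0.6 | 0.80 | 0.74 | 0.83 | 0.83 | 0.90 |
| 0.7 | 0.85 | 0.74 | 0.80 | 0.92 | 0.95 |
| 0.8 | 0.90 | 0.74 | 0.78 | 0.98 | 0.99 |
| 0.9 | 0.95 | 0.74 | 0.76 | 1.00 | 1.00 |

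In change-SD units, ANCOVA needs 62.8 × (1+ρ)/2 per group for power 0.80: 48, 51, 54, 57 and 60 down the table, against 63.

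**If all three visits enter one interaction test** (one possible reading). It has 2 degrees of freedom and noncentrality (n/2)Σd²/(1 − ρ), where d is the deviation of each visit's group difference from the mean over visits. With a T1 difference of 0.50√[2(1 − ρ)], ρ cancels:
- gain fully kept or fully lost at T2: 27.5 × 0.50 × 2/3 = 9.17, power 0.77
- half the gain kept at T2: 27.5 × 0.50 × 1/2 = 6.88, power 0.64.

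The 0.77 is level with ANCOVA at ρ = 0.8 (0.78) and marginally above it at ρ = 0.9 (0.76), so this test is not uniformly weaker.

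No power is attached to the MANOVA, because the article does not say whether its variates are domains or visits.

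**The case against.** The strongest reply is that the planned interaction is already on target. The trial is sized on a difference in increase, and the article says that the interaction tests for larger change in EG. On T0 and T1, that is the sized quantity. Under randomisation, change score and ANCOVA are both unbiased for the same effect. This stands, and it limits the point to efficiency and to the choice of a single estimate.

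Three stronger readings are tempting, and the article does not support them as fact:
- **That the main tests miss the sized contrast altogether.** This fails for the interaction, for the reason just given.
- **That the interaction must span T0, T1 and T2, mixing end-of-treatment with four-month effects.** Statistical analysis does not say which visits enter the model, and Assessments describes changes in pairs.
- **That the MANOVA group term averages in baseline, where the true difference is zero, and so has very low power.** Pooling over visits is not stated; the variates could equally be the seven domains.

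It can also be said that this is a journal article, that its list of methods is open-ended, and that covariates are commonly left to the analysis plan, which is not shown. Silence on covariates alone would be no finding. But the article does name its main tests and gives ANCOVA a different role, so recommending a better main test answers what is written.

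Finally, a baseline-adjusted formula would return 55 per group at ρ of about 0.75 (change SD) or 0.35 (score SD). A reader might infer that adjustment was already built in. The article states no correlation and describes a plain comparison of two groups, so that cannot be assumed.

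**Conclusion.** The point holds as a recommended improvement in precision and clarity. It does not show bias or an invalid analysis. The MANOVA gives no single estimate of the contrast used for sizing. The group-by-time ANOVA can give one, but less precisely than an analysis with baseline as covariate.

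In change-SD units at 55 per group, the gain over the change test runs from about 11 percentage points of power at ρ = 0.5 to about 2 at ρ = 0.9. At ρ of 0.7 or below it brings power to 0.80 or more. In score-SD units the gain is the same at ρ = 0.5, about 3 points at ρ = 0.7, and negligible at ρ = 0.9, where both tests are already well powered. These sizes rest on the assumed ρ. The direction does not, because (1+ρ)/2 is below 1 for any ρ < 1. Compared with a three-visit test, the advantage depends on how much of the effect persists at T2 and can vanish.

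**What to change.** State one primary arm comparison: the EG minus CSG difference at T1, adjusted for the T0 value of the same MCCB score, reported with its 95% CI. Either an ANCOVA or the T1 contrast of a mixed model with baseline as covariate will do; name one. Keep the MANOVA and the group-by-time ANOVA as supportive analyses, and use the same baseline-adjusted form for the secondary outcomes. If the full analysis plan already specifies this, the published text only needs to be brought into line.

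The cost is wording. Baseline MCCB is scheduled for every participant before randomisation, so no extra participants, visits or tests are needed. The choice should be fixed before outcomes are compared by arm.

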### Data storage and use of statistical tools

The data will be stored and analyzed in the Vestfold Hospital Trust using the Statistical Package for the Social Sciences (SPSS version 18.0.1, SPSS inc., Chicago, IL, USA). Data cleaning will be performed via SPSS syntax operations (SPSS Inc., Chicago, IL, USA).

### Ethical considerations

The project is approved by the Regional Ethics Committee of Southern and Eastern Norway (REK Sør-Øst) under file number 2014/372/REK SØR-ØST C. Trial registration has been carried out at ClinicalTrial.gov (NCT02205684). Informed and written consent is a pre-requisite for participation. Initial information about the study will be given to eligible patients by the regular staff during a routine appointment in the outpatient clinic, or by a project co-worker. Further detailed written and oral information about the trial will then be given by the project co-worker. It will be assured that participation is voluntary, that the participants can withdraw at any time point and will receive ordinary treatment whether they choose to participate or not. If the patient understands the nature of the research and is willing to participate, he or she will be asked to sign a consent form. The interviews in the trial will be completed in several encounters with the participant, and emphasis will be put on avoiding unnecessary strain on the individual and adjustment to own preferences. Similarly, when taking part in the treatment intervention, attention will be paid to the physical fitness of the participant. Potential alteration of the intensity and frequency of the physical activity will be adjusted individually over several weeks. Participants experiencing discomfort or possible medical complications while exercising on the treadmill will receive immediate necessary examination by medical staff in the unit. Positive as well as negative results will be published according to the Consolidated Standards of Reporting Trials (CONSORT) guidelines [75].

### Motivational work

Motivating patients with severe mental disorders, prone to be insufficiently physically fit to perform high-intensity interval training twice a week, is perceived a major challenge. Although the motivational work is performed by the intervention staff in informal settings when talking to participants before and after each session, as well as during transportation between their home and the project facilities, it needs to be structured and theory-based. Key constructs in social cognitive theory [76] are applied (i.e. opportunities to perform physical activity; social support for physical activity; confidence to do physical activity; expected benefits and costs of performing physical activity; knowledge and skill to perform physical activity; personal goal setting and monitoring of physical activity), putting much effort in translating this knowledge into effective practices.

### Adverse events

Medical examination and ECG are performed before the exercise program starts, and all patients are evaluated as suitable for training. One potential concern might be the combination of physical exercise and medication, but there is no evidence for danger in exercising while using therapeutic doses of psychotropic medication [77].

### Emergency procedures

To minimize the risk of medical emergencies, patients with a known unstable heart condition (e.g. unstable angina pectoris and recent myocardial infarction) will be excluded from the study. Also, ECG and physical examination performed by a physician are performed before inclusion in the study. Health staff with specific knowledge of cardiopulmonary resuscitation will be present at all treadmill-sessions of physical testing and exercise. In case of symptoms such as chest pain and dizziness during exercise, the session will be discontinued immediately. In case of symptoms of cardiac arrest (unresponsive person with no or abnormal breathing), cardiopulmonary resuscitation will be initiated immediately and an ambulance will be called.

## Discussion

Physical activity has been shown to reduce symptoms of depression and increase cognitive functions in other groups associated with cognitive dysfunction such as Parkinson’s disease [78, 79] and old age [80–82]. It is, therefore, plausible that physical activity may have beneficial effects, both on the level of mental symptoms and cognitive function in schizophrenia, but high-quality data from RCTs is lacking. In the present study high-intensity treadmill exercise for 12 weeks is compared to computer-based skills training, otherwise shown to have beneficial effects on cognitive function [33]. Well-validated measures of the respective functional domains serve as main outcome measures and assessments are performed pre-training, immediately after completed training and 4 months post-treatment allowing appraisal of possible delay between increased CRF and reduced symptoms. Secondary outcome measures are related to factors reducing risk of metabolic syndrome and improving physical health. If we find that intensive exercise can reduce symptoms and increase cognitive performance, it may have implications for future treatment of patients with schizophrenia. As cognitive remediation programs so far have focused on learning techniques in a top-down fashion [83], documenting possible bottom-up beneficial effects may open up new routes for helping these patients increase their cognitive functions. In regard to symptom reduction, broadening the armamentarium of methods, primarily consisting of pharmacological treatment and psychotherapy, to also contain physical activity, will be welcomed as increased CRF in general has an effect on both morbidity and mortality.

As the general optimism regarding the positive effects of physical activity on symptoms and cognition has now spread from normal aging, treatment of depression to schizophrenia, resulting in small-scale or non-systematically researched interventions, the findings of no differential increase in mental and cognitive functions, may lead to some disappointment regarding the role of physical activity in treating these elements of severe mental disorder. Early death from cardiovascular disorders and reduced function due to low cardiovascular capacity and low muscular strength are other important treatable elements of the schizophrenia group of disorders. It is important that treatment approaches are empirically-based and not merely plausible inferences from knowledge in other groups. High-intensity exercise is demanding for the patient, as well as the help-giving system. Thus, with this level of knowledge, emphasis should be placed on finding causal effects or mediating mechanisms, while the cost-effectiveness of physical activity, as a way to improve functions other than key symptoms in schizophrenia, is another important issue.

Perhaps, the greatest challenge conducting an intervention study of this kind is making the participants adhere to the demanding exercise regime. To meet this challenge, participants are given individual tutoring and motivational talks and are offered project-initiated transportation in order to increase adherence – a support regime which is equally comprehensive in both groups. Thus, the present trial involves a support system that would not be sustainable in ordinary clinical work.

In selection of an adequate control condition, it is important for adherence to the skills training control group that both the participants and the intervention staff find the activity meaningful, and by that preventing an expectancy-related lack of effect in the comparison group.

## Trial status

The recruitment started August 2014. By April 2015 a total of 32 subjects were participating. Five subjects have dropped out of the study. The planned recruitment of 126 participants will be completed by October 2016.

## Abbreviations

AES: Apathy Evaluation Scale
ANOVA: analysis of variance
AUDIT: Alcohol Use Disorder Identification Test
AUS: Alcohol Use Scale
BAVQ-R: The revised Beliefs About Voices Questionnaire
BCIS: Beck Cognitive Insight Scale
BDNF: brain-derived neurotrophic factor
BMQ: The Believes about Medicines Questionnaire
CDSS: Calgary Depression Scale for Schizophrenia
CSG: Computer Gaming skills Group
CGI: Clinical Global Impression Scale
CONSORT: Consolidated Standards of Reporting Trials
CRF: cardiorespiratory fitness
CVD: cardiovascular disease
DSM-V: *Diagnostic and Statistical Manual of Mental Disorders*
DUDIT: Drug Use Disorder Identification Test
DUS: Drug Use Scale
ECG: electrocardiogram
EDTA: ethylenediaminetetraacetic
EG: exercise group
EPHAPS: Effects of Physical Activity in PSychosis
EuropASI: European Addiction Severity Index
FTND: Fagerström Test for Nicotine Dependence
GAF: Global Assessment of Functioning
GAI: General Ability Index
HIIT: high-intensity interval training
IPAQ: International Physical Activity Questionnaire
IS: Insight Scale
ISI: Insomnia Severity Index
MANOVA: multivariate analysis of variance
MCCB: Matrics Consensus Cognitive Battery
NTNU: Norwegian University of Science and Technology
NVDPS: Nordre Vestfold Distrikt Psykiatrisk Senter
PANAS: Positive and Negative Affects Schedule
PANSS: Positive and Negative Syndrome Scale
PSYRATS: The Psychotic Symptom Rating Scale
RCT: randomized controlled trial
REK Sør-Øst: Regional Ethics Committee of Southern and Eastern Norway
SCID-I: The Structural Clinical Interview DSM-IV for axis I disorders
SCLOF: Strauss Carpenter Level of Functioning Scale
SVDPS: Søndre Vestfold Distrikt Psykiatrisk Senter
VO_2max_: maximal oxygen uptake
WAIS: Wechsler Adult Intelligence Scale
WHO: World Health Organization
